### Sample size calculation

A sample size determination was conducted for the main outcome variable, the incidence of PONV, using R environment version 13.2 with the gsDesign package. A preliminary retrospective analysis of 100 patients revealed a total incidence of PONV of 48% (unpublished data), confirming previous studies [39]. Based on a power of 0.80 (p = 0.05, two-sided) to detect a 50% reduction in the incidence in PONV (48% vs. 24%) as the clinically relevant treatment advantage between two balanced arms, a total of 123 patients were required for a fixed design. To account for deviations from the expected effect size and incidence due to the avoidance of opioids for postoperative pain relief, a group sequential design was implemented with one interim analysis after 70 patients have completed the study treatment. In a symmetric, two-sided group sequential design with an O’Brien-Flemming alpha spending function [40], the inflation factor was 1.006. The adjusted sample size was estimated to be a total of 124 patients (62 patients per arm). With an assumed rate of 18% protocol violations (derived from a preliminary retrospective analysis of 100 patients), the calculated total sample size was 152 patients (76 patients per arm). To recruit this number of patients, a 30-month inclusion period was anticipated.

### Interim analysis

An interim analysis is planned to assess the primary outcome and the safety of the treatment after 70 patients. For the interim analysis, the data manager will provide the data to the trial statistician with coded treatment assignments (A, B). The statistician will provide summary tables of grade 3 and 4 SAEs and a blind analysis of the primary outcome. Based on these data, the trial chairperson and co-chairperson will decide whether to continue the trial without modifications, continue the trial with modifications or halt the trial due to safety or efficacy concerns. Only if the results are insufficient for that decision the treatment assignments will be revealed and the data will be analyzed again. Unless the benefit of the treatment is demonstrated “beyond a reasonable doubt” by the interim analysis, no formal discontinuation due to efficacy is foreseen. The decision about trial continuation will be based not only on the statistical results but also on clinical judgment [41]. The statistical boundary, requiring p < 0.0039 at the interim analysis to halt due to efficacy, will serve as a guide. The results of the interim analysis will be confidential and strictly limited to the trial statistician, trial chairperson and trial co-chairperson. To avoid bias in the subsequent trial, the results of the interim analysis will be treated confidentially and will not be communicated to the outside or to the clinical investigators involved in the trial.

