## Background

### Scientific background and explanation of rationale

Postoperative nausea and vomiting (PONV) is a common and distressing problem that affects 20-30% of surgical patients after general anesthesia [1]. PONV not only reduces patient comfort but can also lead to serious postsurgical complications, such as dehydration, electrolyte imbalances, the aspiration of the gastric contents, esophageal rupture, suture dehiscence and bleeding [2-9]. Furthermore, PONV significantly affects healthcare costs by prolonging hospital stays [10,11]. In particular, patients undergoing thyroidectomy exhibit a high incidence of PONV, which can be as high as 80% [2,12,13]. PONV after thyroidectomy is most likely caused by edema and inflammation around the neck tissues, leading to evoked parasympathetic impulses through the vagus, recurrent laryngeal and glossopharyngeal nerves to the vomiting center [13-15].

Dexamethasone, a glucocorticosteroid, has been described as highly effective against chemotherapy-induced nausea and vomiting [16,17]. A recently published study comparing the efficacy of six well-established antiemetic strategies concluded that the use of dexamethasone as a first-line method of prophylaxis for PONV is a reasonable treatment option [18]. The exact mechanism by which dexamethasone exerts its antiemetic activity is not well understood. The antagonizing effect of corticosteroids on inflammatory reactions and the dexamethasone-triggered release of endorphins, which results in mood elevation, a sense of well-being and appetite stimulation, may contribute to this effect [19-21]. Due to their anti-inflammatory activity, corticosteroids have been shown to reduce postoperative swelling, pain and sore throat [22-25]. Despite these advantages, the perioperative use of dexamethasone for the prophylaxis and treatment of PONV has not been established [26], possibly due to concerns that the use of corticosteroids would increase susceptibility to infections. However, several studies have indicated that even long-term corticosteroids treatments do not lead to a significant increase in wound infections [27-29]. Another possible reason is the lack of awareness about the antiemetic effect of this type of medication.

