All grade 4 or 5 AEs will be counted as SAEs, with the exclusion of PONV (as the primary outcome), delayed wound healing (as a secondary outcome) and wound infection (as a secondary outcome). Additionally, postoperative hypoparathyroidism and lesions to the recurrent nerve will not be counted as SAEs because they are considered imminent risks of a thyroidectomy.

The local Ethics Committee and Swissmedic will be informed by the principal investigator about SAEs according to local legislation (VKlin/HMG). A yearly safety summary will be provided to the local Ethics Committee and Swissmedic.

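### The interim safety tables, as specified, leave out wound infection and wound healing, and their grade range does not match the SAE definition

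*Protocol article*

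**What the plan says.** The Interim analysis section gives the look two purposes: "An interim analysis is planned to assess the primary outcome and the safety of the treatment after 70 patients". The statistician receives the data with arms coded A and B. The output is then specified: "The statistician will provide summary tables of grade 3 and 4 SAEs and a blind analysis of the primary outcome". The decision is tied to that output: "Based on these data, the trial chairperson and co-chairperson will decide whether to continue the trial without modifications", with modification or a halt for safety or efficacy as the alternatives. There is one fallback: "Only if the results are insufficient for that decision the treatment assignments will be revealed and the data will be analyzed again".

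The Outcome measurements section says what an SAE is. Adverse events of grade 4 or 5 count, "with the exclusion of PONV (as the primary outcome), delayed wound healing (as a secondary outcome) and wound infection (as a secondary outcome"). It also exempts hypoparathyroidism and recurrent nerve lesions after surgery. The same section makes two kinds of outcome secondary: wound healing, assessed at discharge and at six weeks, and a list of in-hospital morbidity that includes wound, lung and urinary infection, bleeding and reoperation.

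The Background says that perioperative dexamethasone has not become established, "possibly due to concerns that the use of corticosteroids would increase susceptibility to infections". It then cites studies in which even long-term corticosteroids did not significantly raise wound infection.

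**The concern.** An SAE category built with outcome-based exemptions is reused as the whole safety content of the interim look. The exemptions are explained by the fact that these events are trial outcomes. That may suit SAE reporting, but it does not suit a decision on whether to continue. PONV is exempt for the same reason and comes back as the primary outcome analysis. Wound infection and delayed wound healing do not come back anywhere in the stated package.

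At stake is the only planned look by arm before the final analysis. The chairs could continue without modification on a sparse SAE table, while any imbalance in wound outcomes stays untabulated although the data are on the case report forms. The mismatch in grades makes the table sparser still and leaves fatal events outside the stated range.

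**Working it through.** **Step 1: which events reach the interim tables.** Inputs are the SAE definition and morbidity list (Outcome measurements) and the table content (Interim analysis).

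| Event | Grades 1–3 | Grade 4 | Grade 5 |
|---|---|---|---|
| Wound infection, delayed wound healing | not an SAE (below threshold) | exempt | exempt |
| Recurrent nerve lesion, hypoparathyroidism | not an SAE | exempt | exempt |
| Other morbidity items (e.g. lung or urinary infection, bleeding, reoperation) | not an SAE | SAE, tabulated | SAE, but outside the stated range of 3 and 4 |

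Of the named morbidity items, only wound infection and laryngeal nerve lesion overlap with the exemptions. The rest are kept out only when they fall below SAE grade.

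**Step 2: does the answer depend on which grade range is meant?** There are three readings:

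- Both passages taken literally: the overlap is non-exempt grade 4 events only.
- The interim range governs: non-exempt grade 3 and 4 events appear and grade 5 does not.
- The SAE definition governs: non-exempt grade 4 and 5 events appear.

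Under all three, taking the exemptions to carry over, wound infection and delayed wound healing are absent. Settling the grade range therefore does not settle the wound outcomes, so both repairs are needed.

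**Step 3: the plan's own figures.** The point does not rest on the sample size, but the total is used below, so it was checked. For 48% vs 24%, two-sided 0.05, power 0.80, pooled variance and no continuity correction, n = 61.6 per arm, or 123.2 in total (plan: 123). Then 123.2 × 1.006 = 123.9 (plan: 124), and 124 / 0.82 = 151.2, rounded up to an even 152 (plan: 152).

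**Step 4: illustration of size.** The documents give no rates for wound events or SAEs, so the rates below are assumptions. With 1:1 allocation, 70 patients give about 35 per arm.

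The chance of at least one wound infection in an arm is 1 − (1 − p)^35:

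| Assumed p | 1% | 2% | 5% | 10% |
|---|---|---|---|---|
| Probability | 30% | 51% | 83% | 97% |

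The tables as specified would show none of these events.

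The chance that the SAE table is empty in all 70 patients, if 0.5% or 1% have a countable SAE, is 0.995^70 = 0.70 or 0.99^70 = 0.495.

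Patients not yet counted at the look: 152 − 70 = 82, and 82 / 152 = 54%. This is an upper limit on those enrolled after the decision, because the documents do not say that recruitment pauses.

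**Step 5: what the extra tables could show.** Fisher exact power at 35 per arm (two-sided 0.05) is about 7% for 2% vs 10% and 53% for 2% vs 20%. A formal test would rarely settle anything. The use is descriptive, which fits a decision that the protocol rests partly on clinical judgment.

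**The case against.** The strongest reply is that other safeguards exist. The data reach the statistician with coded arms, and the codes can be revealed and the data analyzed again. Case report forms are reviewed by the trial chair or a delegate, and a monitor reviews their medical content. The chairs can have a patient unblinded because of an AE, and a yearly safety summary goes to the Ethics Committee and the regulator. This stands against any claim that the chairs cannot see wound outcomes by arm. A reader might infer that from the interim section, but the text does not support it. What the text shows is that they are not given them: none of these provisions says that wound outcomes are added by arm. Revealing the codes identifies the arms and adds no outcome.

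A reader might also infer that the whole morbidity list is shut out. It is not: lung infection, urinary infection, bleeding, reoperation and the rest count at grade 4 or 5 unless exempt.

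A third stronger reading is that the protocol itself regards infection as the main hazard. The Background offers it only as a possible reason why others have not adopted the drug, and answers it for wound infection. The protocol also does not say that the morbidity outcomes were chosen for that reason.

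Finally, an article may leave table layouts to the full protocol or analysis plan. That would answer a complaint about missing detail. Here, however, the article states the content of the safety report and ties the decision to it, so the exclusion follows from what is written.

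**Conclusion.** The point holds as a cheap improvement to safety monitoring. As written, the interim decision rests on SAE tables from which wound infection and delayed wound healing are removed at every grade, while the remaining morbidity items appear only at SAE grade. Separately, the range in the interim section (3 and 4) and the SAE definition (4 or 5) contradict each other and must be reconciled; at present grade 5 events are outside the tables.

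The size cannot be fixed from the documents. Under assumed wound infection rates of 1% to 10%, an arm of about 35 would have at least one event with probability 30% to 97%, none of it shown. No sample size, alpha or result of the primary analysis is affected. The conclusion assumes that the interim report contains what the protocol says it contains and that the SAE exemptions apply to it.

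**What to change.** In the Interim analysis section, add one sentence: the report will also give descriptive tables by coded arm (A/B) of wound infection, wound healing at discharge and, where available, at six weeks, and each other in-hospital morbidity outcome at any grade. In the same edit, reconcile the grade range there with the SAE definition under Outcome measurements, so that grade 5 events are not left out of the tables.

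The cost is a few tables from data already on the case report forms. Six-week wound data will be incomplete for the latest patients, because the look is triggered when 70 have completed study treatment. The tables should be labelled descriptive, with no test or boundary attached, given the low power at about 35 per arm.

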### Outcome measurements

The primary outcome will be the incidence of PONV, which will be assessed at postoperative hours 4, 8, 16, 24, 32 and 48. A patient will be considered to suffer from PONV if nausea or vomiting is documented at any of the postoperative assessments.

One secondary outcome will be the severity of the PONV, measured with a score ranging from 0 to 3 (0 for no nausea; 1 for mild nausea, defined as nausea requiring a single administration of an antiemetic drug; 2 for severe nausea, defined as nausea requiring the repeated administration of antiemetic drugs; and 3 for nausea leading to vomiting).

Other secondary outcomes will be the intensity of pain at rest and under provocation (while rotating the neck 90° to each side), measured at postoperative hours 4, 8, 16, 24, 32 and 48 with a Verbal Rating Scale (VRS) ranging from 0 to 10, with 0 considered to be no pain and 10 considered to be the worst pain imaginable. Additional secondary outcomes will include the length of hospital stay (measured as the number of hours after the intervention), wound healing at the time of discharge and six weeks after the intervention, the amount of anesthetic medication required (total amount of administered fentanyl, remifentanil, rocuronium measured in mg and the total amount of administered remifentanil measured in μg) and postoperative in-hospital morbidity, including wound infection, reoperation, bleeding, prolonged intubation, laryngeal nerve lesion, urinary retention, urinary tract infection, pulmonary infection and gastrointestinal hemorrhage or newly occurring insulin dependence in diabetic patients.

For the safety analysis, adverse events (AEs) and serious adverse events (SAEs) will be evaluated. The patients will be instructed by the investigator to report the occurrence of any AE, defined as an unfavorable and unintended sign, symptom or disease temporally associated with the treatment provided in the present trial. The investigator (treating physician) will be asked to verify the absence or presence of all the AEs predefined on the CRF. Information in the patients’ medical files will be reported using the Common Terminology Criteria for Adverse Events v4.03 (CTCAE 4.03) coding system, rather than a narrative description. AEs will be scored as grade 1 (a mild AE) to grade 5 (death related to the AE), and a causality assessment will be performed.

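### The interim safety tables name SAE grades that do not match the protocol's own SAE definition: grade 3 is empty as defined, grade 5 (death) is left out, and wound events are exempt at every grade

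*Protocol article*

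**What the plan says.** The relevant statements in the protocol article are these.

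- **Grading** (Outcome measurements): "AEs will be scored as grade 1 (a mild AE) to grade 5 (death related to the AE". The CTCAE 4.03 system is used for coding.
- **SAE definition** (Outcome measurements): "All grade 4 or 5 AEs will be counted as SAEs", apart from named exemptions. Three are exempt because they are trial outcomes: PONV, "delayed wound healing (as a secondary outcome) and wound infection (as a secondary outcome". Two more are exempt as recognised risks of the operation: "postoperative hypoparathyroidism and lesions to the recurrent nerve will not be counted as SAEs". None of the exemptions carries a grade limit.
- **SAE notification** (Outcome measurements): SAEs go to the Ethics Committee and Swissmedic under local law, with a yearly safety summary.
- **Interim safety output** (Interim analysis): "The statistician will provide summary tables of grade 3 and 4 SAEs and a blind analysis of the primary outcome". The statistician works with arms coded A and B. On these data the chairperson and co-chairperson choose whether to carry on unchanged, carry on with changes, or stop for safety or efficacy.
- **Background**: in explaining why perioperative dexamethasone is not established, the article says this is "possibly due to concerns that the use of corticosteroids would increase susceptibility to infections". The next sentence cites studies that found no significant increase in wound infections even with long-term treatment.

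**The concern.** The interim analysis has safety as one of its two stated purposes, and the SAE tables are the only safety display named for it. Their grade range disagrees with the SAE definition given a few sections earlier, and it disagrees at the top of the scale, where a single event can matter most. A statistician who programs the tables to the letter would produce a grade 3 category that cannot be filled and no category for deaths.

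The exemption adds to this. Wound infection is a form of the harm that the Background raises for this drug class. Because the exemption has no ceiling, even a fatal wound infection is not an SAE as worded and so cannot enter a table of SAEs. Treating an event as a trial outcome is an understandable reason not to report ordinary cases as SAEs. The article does not say whether the gravest cases were meant to be covered as well.

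At stake is whether the two people who take the decision see an imbalance between arms in deaths or grave wound events in the summary prepared for them.

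**Working it through.** No formula applies, and the plan gives no figure to reproduce. The check compares sets of grades.

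**Step 1: grades.**
- SAE grades by definition (Outcome measurements): {4, 5}
- Grades in the interim tables (Interim analysis): {3, 4}
- In both: {4}
- Tabulated but not SAE grades: {3}, so this category is empty under the stated definition
- SAE grades not tabulated: {5}, death related to the AE

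**Step 2: what happens to each kind of event as the text stands.**

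| Event | SAE by the protocol's definition? | Notified individually as a protocol-defined SAE? | In the interim SAE tables? |
|---|---|---|---|
| Grade 3, not exempt | no | no | no (category named, but empty) |
| Grade 4, not exempt | yes | yes | yes |
| Grade 5, not exempt | yes | yes | **no** |
| Wound infection or delayed wound healing, grade 4 | no | no | **no** |
| Wound infection or delayed wound healing, grade 5 | no | no | **no** |

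The third column applies the protocol's own definition. Local law may define an SAE differently, but the article does not reproduce that definition.

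**Step 3: does another section close the gap?** Wound infection is collected as in-hospital morbidity, and wound healing is assessed at discharge and at six weeks. Both are compared by a chi-square test (Outcome measurements, Statistical analysis). Neither is listed among the interim outputs. PONV is also exempt, but as the primary outcome it has its own interim analysis, so the wound events are in a different position.

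**Step 4: does the result depend on how the definition is read?** The definition does not say that only grades 4 and 5 are SAEs. If some unstated criterion could make a grade 3 event an SAE, the grade 3 category would not be empty. Grade 5 would still be missing, so the main part of the finding holds on either reading.

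**Step 5: what might have been meant?**
- SAEs of grades 4 and 5: deaths would appear, but exempt wound events would not.
- AEs of grades 3 to 5: both would appear, because the exemption is from the SAE category and not from being an AE.
- AEs of grades 3 and 4: wound events up to grade 4 would appear, but deaths would not.

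The three candidates give different tables, and the text does not settle which was intended.

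**The case against.** The strongest reply is that this is a slip in one sentence and that nobody would be kept unaware of a death. Much of that stands. Non-exempt grade 5 events are SAEs and are notified individually. The chairperson or co-chairperson also judges whether AEs or SAEs call for unblinding a patient (Blinding), and the trial chair or a delegate reviews the data (Setting and data collection locations). The interim decision may draw on clinical judgment as well as on the statistical results, and the assignments can be revealed if the coded results do not suffice. A reader might infer that deaths are concealed from the decision-makers or the authorities. The documents do not support that. What the reply does not supply is the comparison by arm: single notifications are not a summary by coded arm, and that summary is what the interim section specifies.

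On the wound events, the exemption is a stated choice with a stated reason, and the data are still collected and compared between arms. A reader might infer that wound infection goes unrecorded, or that the Background treats it and delayed healing as established harms of the drug. Neither inference holds. The Background names susceptibility to infection only, offers it as a possible explanation, and then discounts it. Nor does the article describe grade 4 as life-threatening; it spells out only grades 1 and 5. What remains is that the exemption has no ceiling and that nothing brings these events into the interim review.

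That the article condenses a fuller protocol does not answer the point. This is not a detail left out but two explicit statements that disagree.

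**Conclusion.** The finding holds in a limited form. The interim tables and the SAE definition share only one grade: one of the two tabulated grades is empty as defined, and one of the two SAE grades, the one for death, is not tabulated. Separately, wound infection and delayed wound healing of grade 4 or 5 lie outside the SAE set and therefore outside the interim tables.

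The defect is confined to the specified interim safety summary and, for the exempt wound events, to the protocol's own SAE category. No rate is given from which to estimate expected counts; they are likely to be small among 70 patients. The interim and final alphas (0.0039 and 0.0488), the 80% power and the 152 patients are unaffected. The point is worth correcting because this is the only safety table named for a decision that includes stopping, and because the correction costs little.

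The conclusion assumes that the tables would be produced as worded and that wound events are graded like other AEs. Exempting them from a rule on grade 4 and 5 AEs presupposes the latter.

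**What to change.** Reconcile the Interim analysis and Outcome measurements sections.

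1. In Interim analysis, specify tables by coded arm of all AEs of grades 3, 4 and 5, naming deaths explicitly and including the wound events that are exempt from the SAE definition.
2. In Outcome measurements, state explicitly whether the exemption for wound infection and delayed wound healing is meant to cover grades 4 and 5. A ceiling is meaningful only at those grades, because lower grades are not counted as SAEs under the stated grade rule in any case.

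The cost is a few words in two sections and a few extra table rows. No new visit or randomised patient is needed, and the coded-arm arrangement stays as it is. The change should be made before the interim tables are produced.
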